#### Outcome measures

##### Primary outcome

Parental self-efficacy regarding the parent’s own ability to promote healthy lifestyle behaviours in their five-year old child is the primary outcome. This is assessed using an electronic version of the validated `Parental self-efficacy for promoting healthy dietary and physical activity behaviours in their children´ questionnaire. This questionnaire includes 16 questions divided into three factors (i.e., self-efficacy for promoting healthy dietary behaviours in children, self-efficacy for limit-setting of unhealthy dietary or physical activity behaviours, and self-efficacy for promoting healthy physical activity behaviours) [14]. This questionnaire will be filled in online by the same parent (i.e., the parent that accompanied the child to the five-year check-up) at baseline and post-intervention (i.e., two months after the five-year check-up).

##### Secondary outcomes

A modified version of the Swedish National Board of Health and Welfare’s survey regarding health behaviours [15] is used to assess dietary outcomes. The amount of fruits and vegetables are assessed as the average number of standardized portions per day over the past month, and the intake of sweet beverages as the average frequency per day. The amount of time spent watching screens (e.g., phones, tablets, TV, and computer) is assessed in minutes per day on a typical day that the child is at home and not at pre-school.

At baseline, the accompanying parent will also complete a brief electronic demographic questionnaire which includes questions regarding their age, sex, and socioeconomic position as well as their child’s date of birth, sex, country of birth, weight, and height (measured at the five-year check-up).

##### Sample size

We calculated the sample size required to achieve a statistical power of 80% to detect a four-point difference in parental self-efficacy between the two treatment groups. The power was for a Wald test of the coefficient of the group variable in linear random intercept model where the 6-month change in outcome is the dependent variable and the group indicator is the only covariate. The linear random-intercept model included a center-specific normal random intercept, which accounted for the within-center stochastic dependence of the data. The estimated sample size was obtained by generating 1000 pseudo-random Monte-Carlo samples under an assumed intra-center correlation of 0.03 and the two specified group differences. The assumed fixed regression coefficients and the regression residual variance were estimated using unpublished parental self-efficacy data from the MINISTOP trial [16]. A total of 368 parent child dyads (*n* = 184 per arm) are needed. Assuming a 20% drop-out rate [16, 17], a minimum of 450 children will be recruited, i.e., 225 per group.

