**Methods:**

A hybrid type I effectiveness-implementation trial will be conducted. A cluster randomized controlled trial will be used to assess the effectiveness of `Saga Stories in health talks´ in 42 CHC centers across six regions in Sweden. `Saga Stories in health talks´ consists of material for CHC nurses to use to facilitate the health talk with both the child and parent(s) and is complemented with take-home material. Parent and child dyads are recruited (*n* = 450) from participating CHC centers when they attend their 5-year routine visit. The intervention group receives the health talk using Saga Stories and take-home material, whereas the control group receives the standard health talk. The primary outcome is parental self-efficacy to promote healthy diet, physical activity, and screen time behaviours in their child and secondary outcomes include children’s intake of key dietary indicators and screen time. All outcomes are assessed at baseline and 2-months post-intervention. The implementation outcomes that will be assessed are: acceptability, appropriateness, feasibility, satisfaction, usage, fidelity, adoption, and sustainability (assessed quantitatively and qualitatively).

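### The power calculation is described for a 6-month change, but the primary outcome is followed up only at 2 months, so the stated 80% power and 368 dyads are not shown to apply to the trial's endpoint

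*Protocol article*

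**What the plan says.** All of this is in the protocol article.

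- **Sample size, target.** The trial is sized for a "statistical power of 80% to detect a four-point difference in parental self-efficacy between the two treatment groups".
- **Sample size, model.** The test is a Wald test of the group coefficient in a "linear random intercept model where the 6-month change in outcome is the dependent variable", with a centre-specific random intercept.
- **Sample size, simulation settings.** The 1000 simulated samples were drawn under an "assumed intra-center correlation of 0.03 and the two specified group differences". Four points is the only difference the paragraph gives.
- **Sample size, source of the variance.** The fixed coefficients and the "regression residual variance were estimated using unpublished parental self-efficacy data from the MINISTOP trial". Neither the SD nor the time point of those data is given.
- **Sample size, result.** 368 dyads, 184 per arm.
- **Abstract, Methods.** "All outcomes are assessed at baseline and 2-months post-intervention".
- **Primary outcome.** The same parent completes the self-efficacy questionnaire "at baseline and post-intervention (i.e., two months after the five-year check-up").
- **Table 1.** The post-allocation and close-out columns are both at 2 months. There is no later column.

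**The concern.** The sample size section defines the powered quantity over one interval, and every other section that dates the follow-up of the primary outcome gives another. No text explains why a 6-month quantity should stand in for a 2-month one. The mention of two group differences where one is given is a second sign that the paragraph does not match this trial.

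The interval matters for two reasons. With equal variances at both times, a change score has variance 2σ²(1 − ρ), where ρ is the correlation between baseline and follow-up. That correlation can differ between 2 and 6 months. The between-group difference that can be expected may also depend on how long after the visit it is measured.

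This paragraph is the only justification for the trial's size, and it is what a reader would turn to when interpreting a null primary result. If the powered quantity is not the measured one, the 80% cannot be relied on for that purpose.

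**Working it through.** **1. The time points side by side**

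| Place in the protocol article | Follow-up of parental self-efficacy |
|---|---|
| Abstract, Methods | 2 months |
| Primary outcome | 2 months after the five-year check-up |
| Table 1 | 2 months (post-allocation and close-out) |
| Sample size | 6-month change |

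The sample size section is the only one that disagrees.

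**2. Can 368 be reproduced?** Not independently, because no SD is given. The SD can only be back-solved from 368, so the figures below illustrate sensitivity and do not test the plan's number.

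Inputs from the documents: difference 4 points, power 80%, ICC 0.03, 184 per arm, 42 centres randomized (Randomization and blinding). Assumptions: two-sided alpha 0.05 (not stated in the Sample size section), equal centre sizes, and a normal approximation with a design effect in place of the simulation.

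- Dyads per centre: m = 368/42 = 8.76
- Design effect: DE = 1 + (8.76 − 1) × 0.03 = 1.233
- Effective number per arm: 184/1.233 = 149.2
- Implied SD of change: 4 / [(1.960 + 0.842) × √(2/149.2)] = 12.33
- Standardized difference: 4/12.33 = 0.32

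With the 40 centres that remain (22 + 18), keeping 184 per arm and equal centre sizes, m = 9.2, DE = 1.246 and the implied SD is 12.27. The centre count makes almost no difference to this step.

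**3. Sensitivity of power to the 2-month SD.** Let f be the ratio of the 2-month change SD to the back-solved SD. At 368 dyads and four points, power = Φ(2.80/f − 1.96).

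| f | Power |
|---|---|
| 0.8 | 94% |
| 0.9 | 88% |
| 1.0 | 80% |
| 1.1 | 72% |
| 1.2 | 65% |

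The documents do not favour any row.

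**4. Sensitivity to the difference.** With the SD unchanged, power = Φ(2.80 × δ/4 − 1.96). A true 2-month difference of 3 points gives about 56%, and 5 points about 94%.

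**5. A caution on required sample size.** Scaling 368 by f² holds the design effect fixed. With 42 fixed centres, more dyads mean larger centres and a larger design effect. The equation is then N = (368/1.233) × f² × (0.97 + 0.03N/42). At f = 1.1, simple scaling gives 368 × 1.21 = 445, while the equation gives about 472. Neither is a corrected sample size, because f is unknown.

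**The case against.** The strongest reply is that the 6-month figure and the reference to two differences may be leftover wording around a simulation that was in fact run for the 2-month outcome. The article does not say at what time point the earlier trial's data were collected, so this cannot be excluded. Borrowing a variance from an earlier trial is also ordinary planning practice, and even a 6-month variance might be defended as adequate for 2 months. The endpoint, its timing and the analysis model do not depend on this paragraph, so the validity of the effect estimate is not at risk.

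All of that stands. It limits what can be concluded but does not remove the contradiction, which is in the current text. Nor is this a detail that an article may leave to an analysis plan, because the article itself states a horizon and that horizon conflicts with its own follow-up schedule.

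Three stronger readings are tempting, and the documents do not support them:

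- **That the trial is underpowered.** The 2-month change could have a smaller SD than the 6-month change, in which case power would exceed 80%.
- **That the simulation was certainly run for another design.** Only the description is shown to conflict. The code and its input data are not available.
- **That a particular larger sample is needed.** This would require a 2-month SD, which the documents do not give.

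**Conclusion.** The point holds as an internal contradiction. The sample size text describes power for a 6-month change and mentions two group differences, while the trial follows its primary outcome up once, at 2 months, and specifies one difference. The claim of 80% power with 368 dyads is therefore not shown to apply to the primary endpoint.

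The contradiction itself is certain. Its effect on power is not, in either size or direction. The illustrative range of about 94% down to 65%, for a 2-month SD 20% below to 20% above the implied 12.3, rests on two-sided alpha 0.05, ICC 0.03, 42 equal centres and an SD back-solved from the very figure in question. The ±20% limits are chosen for illustration and have no source in the documents.

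**What to change.** Check the simulation code and its input data first, then take one of two routes.

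1. **If the 2-month change was simulated:** correct the 6-month wording and the reference to two group differences. No rerun is needed.
2. **If 6-month data were used:** state the time point and SD of the source data. Then either justify carrying them over to 2 months, or rerun the simulation for the 2-month change with the four-point difference and the 22 + 18 centres now in the trial. Restate the power over an SD range that is symmetric about the assumed value.

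In both cases, state the alpha level and whether the test is two-sided.

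The cost is a check of existing code, corrected wording and at most one rerun. The recruitment target, the endpoint and the procedures stay as they are. The restated power may turn out lower or higher than 80%.

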#### Randomization and blinding

Forty-two CHC centers with 1-7 nurses per center were randomly assigned to the two treatment groups (22 CHC centers in the intervention and 20 in the control group). To ensure balance, we stratified the randomization by geographical regions and center size. Two CHC centers dropped-out before the trial was initiated due to high absenteeism because of the COVID-19 pandemic. Therefore, there is 22 CHC centers in the intervention group and 18 in the control group. Due to the nature of the trial, CHC nurses and participants cannot be blinded; however, outcome assessors are blinded to the treatment allocation of the participating families.

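### At the assumed 20% drop-out, recruiting 450 leaves 360 dyads, 8 short of the 368 the protocol requires: a small slip in the stated figures that should be restated

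*Protocol article*

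**What the plan says.** All of the following is in the protocol article.

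- **Sample size, requirement:** "We calculated the sample size required to achieve a statistical power of 80% to detect a four-point difference in parental self-efficacy". The result is "A total of 368 parent child dyads", that is, 184 per arm.
- **Sample size, recruitment:** "Assuming a 20% drop-out rate [16, 17], a minimum of 450 children will be recruited, i.e., 225 per group".
- **Sample size, method:** the figure comes from 1000 simulated samples with an intra-centre correlation of 0.03 and a Wald test in a random-intercept model. The number of centres, their sizes, the alpha level and the SD are not given. For the variance, the section says only that the fixed coefficients and "the regression residual variance were estimated using unpublished parental self-efficacy data from the MINISTOP trial".
- **Randomization and blinding:** 42 centres were randomised (22 intervention, 20 control) and two withdrew before the trial began. "Therefore, there is 22 CHC centers in the intervention group and 18 in the control group".
- **Abstract, Methods:** effectiveness is to be assessed "in 42 CHC centers across six regions in Sweden", with n = 450.
- **Statistical analyses:** the primary analysis uses completers only, provided the missing data are judged to be missing completely at random.

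**The concern.** A recruitment target should deliver the required number of evaluable participants under the drop-out rate that the plan itself assumes. This one does not. Because the primary analysis is planned on completers, the number left after drop-out is the one that determines power. The loss of two control centres acts in the same direction, and the Sample size section does not say whether the calculation was revisited afterwards. Readers will use this paragraph to judge what a null result means, so its figures should agree with each other and with the trial as it is now constituted.

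**Working it through.** **Step 1: the recruitment figure.** Inputs from the Sample size section are 368 required, 20% drop-out and 450 recruited.

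- Inflation by division: 368/(1 − 0.20) = 460, or 230 per arm.
- Inflation by multiplication (a common mistake): 368 × 1.20 = 441.6, rounded up to 442.
- The stated 450 equals neither. It is 10 below 460 and 8 above 442.
- Completers from 450: 450 × 0.80 = 360, or 180 per arm. The shortfall is 8 dyads, 8/368 = 2.2%.
- Drop-out at which 450 still yields 368: 1 − 368/450 = 18.2%.

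**Step 2: the effect on power.** The 368 itself cannot be reproduced, because the SD, alpha and number of centres are not stated. The check therefore assumes that 184 per arm gives exactly 80% and asks how much is lost from there.

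Inputs from the protocol: difference 4 points, intra-centre correlation 0.03. Assumptions: two-sided alpha 0.05, 22 + 20 centres in the planning simulation, and a coefficient of variation (CV) of centre size of 0, 0.6 or 1.0, held the same before and after the loss.

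Formulas, with n dyads and k centres in an arm and m = n/k:

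- design effect DE = 1 + [(1 + CV²)m − 1] × 0.03
- V = sum over the two arms of DE/n
- power = Φ(4/(SD × √V) − 1.96)

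Calibration with CV = 0:

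- Intervention: m = 184/22 = 8.36, DE = 1.221. Control: m = 184/20 = 9.2, DE = 1.246.
- V = (1.221 + 1.246)/184 = 0.01341, √V = 0.1158.
- SD = 4/(2.802 × 0.1158) = 12.33. With CV 0.6 and 1.0 the calibrated SD is 11.88 and 11.19.

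Worked case, 180/180 in 22/18 centres with CV = 0:

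- Intervention DE = 1.215 (m = 8.18), control DE = 1.270 (m = 10).
- V = 2.485/180 = 0.01381, √V = 0.1175, standard error = 12.33 × 0.1175 = 1.449.
- Power = Φ(4/1.449 − 1.96) = Φ(0.80) = 78.8%.

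| Completers | Centres | Power, CV 0 / 0.6 / 1.0 |
|---|---|---|
| 184/184 | 22/20 | 80.0% (calibrated) |
| 180/180 | 22/20 | 79.3 / 79.4 / 79.4% |
| 184/184 | 22/18 | 79.5 / 79.4 / 79.2% |
| 180/180 | 22/18 | 78.8 / 78.8 / 78.6% |
| 198/162 (360 split by centres) | 22/18 | 78.5 / 78.5 / 78.4% |

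Calibrating to 21 + 21 centres instead changes these results by at most 0.03 points. With a t reference used both in the calibration (40 df) and after the loss (38 df), the last two rows become 78.7% and 78.4% at CV 0.

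**Step 3: simulation error of the plan's own figure.** With 1000 samples at 80%, the standard error is √(0.8 × 0.2/1000) = 1.26 points, so the 95% margin is about ±2.5 points.

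**The case against.** The strongest reply is that nothing of substance turns on this. The body text calls 450 a minimum, the shortfall is 2.2%, and 20% is itself a rounded assumption. The slip alone costs 0.6 to 0.7 points of power. Adding the lost centres brings the loss to 1.2 to 1.6 points, still less than the ±2.5 points of simulation error around the planned 80%. Equal arms also remain feasible, since 18 control centres would need 225/18 = 12.5 recruits each. The abstract's 42 is the number randomised, and the Randomization and blinding section openly explains how it became 40.

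Most of that stands, and it limits the point to a correction of stated figures. It does not remove the inconsistency. A minimum should secure the requirement under the stated drop-out rate. Simulation error concerns how 368 was obtained; it does not affect dividing 368 by 0.80.

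A reader might go further and infer that power is really about 73 to 76%, by adding unequal centre sizes (CV 0.6) and a t reference on 38 df. The documents do not support this. The protocol does not say what centre sizes the simulation used, so inequality may already be included. The comparison is also uneven if these features are added only after the loss. With SD 12.33 and CV 0.6, the intact design of 184/184 in 21/21 centres already falls to 77.1%, against about 75.7% for 180/180 in 22/18 centres, so the slip and the lost centres account for only about 1.4 points. Finally, the protocol specifies a Wald test, and moving from z to t between the two scenarios changes the test.

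**Conclusion.** The point holds as a small inconsistency. The plan's requirement (368), drop-out (20%) and recruitment target (450) cannot all be right together: 450 gives 360, 460 would give 368, and 450 gives 368 only at about 18.2% drop-out or less. This part is plain arithmetic and needs no assumption.

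The power for 360 completers in 22/18 centres is about 78.4 to 78.8%. That rests on a two-sided alpha of 0.05, an SD calibrated to 80% at 184 per arm, and 42 centres in the planning simulation, none of which the protocol states. A reader might infer that the trial is materially underpowered or that the 80% claim collapses; a loss of 1.2 to 1.6 points does not support that. The abstract's 42 centres is an editorial matter.

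**What to change.** Restate the figures in the Sample size section; no extra recruitment is called for. Say that 450 recruits give 360 completers (180 per arm) at 20% drop-out, or 368 at about 18%. Then restate the power for 360 completers in the 40 participating centres (22/18), with the alpha, SD, number of centres and centre sizes used. On the assumptions above the result should be close to 78.5 to 79%. The abstract may note 42 centres randomised and 40 participating.

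The cost is a few words and one rerun of an existing simulation, and the quoted power falls by one to two points. For information only, keeping 80% with 22/18 centres would take about 374 to 382 evaluable dyads, or roughly 468 to 478 recruits at 20% drop-out (374/0.80 to 382/0.80).

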##### Statistical analyses

All analyses will be conducted according to the intention-to-treat method. The primary analysis will be completers only, as long as the missing data is considered missing completely at random. Missing data will be imputed using multiple imputations with chained equations [18]. To contrast differences in parental self-efficacy, dietary intake, and screen time between treatments, we will use linear random-effects models, specifying the CHC center as a random effect to account for clustering. The models will be estimated unadjusted and adjusted for child age (continuous) and sex (boy vs. girl). Interaction analyses will also be conducted to investigate if the interventional effect differs with regards to the participating parents’ age, education status, country of birth, and body mass index (BMI).

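### The primary analysis is completers-only on a judgement of MCAR that data cannot confirm, beside an intention-to-treat claim and an imputation sentence with no stated role

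*Protocol article*

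**What the plan says.** Three consecutive sentences in Statistical analyses deal with who is analysed and how missing data are handled:

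1. "All analyses will be conducted according to the intention-to-treat method".
2. "The primary analysis will be completers only, as long as the missing data is considered missing completely at random".
3. "Missing data will be imputed using multiple imputations with chained equations [18" (the quote ends at the reference number).

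For the comparison itself, "we will use linear random-effects models, specifying the CHC center as a random effect to account for clustering". The models are to be run unadjusted and then adjusted for the child's age and sex. Baseline self-efficacy is not listed as a covariate. The power model under Sample size takes the change in self-efficacy as the dependent variable, with group as its only covariate.

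On expected loss, the Sample size section says "A total of 368 parent child dyads (*n* = 184 per arm) are needed" and then "Assuming a 20% drop-out rate [16, 17], a minimum of 450 children will be recruited, i.e., 225 per group".

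**The concern.** A completers-only primary analysis leaves out enrolled dyads from randomised centres, which sits badly with an intention-to-treat statement covering every analysis. The imputation sentence does not settle the matter, because it is given no role.

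The larger problem is the condition. The primary analysis set depends on whether missingness is considered MCAR, and the article gives no criterion, timing or decision-maker. A check that finds nothing does not show that the data are MCAR.

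There are reasons to doubt MCAR here. Parents are not blinded (Randomization and blinding), and they report the primary outcome themselves online (Primary outcome). At two months, those who had the Saga Stories talk are also asked about satisfaction and usage (Satisfaction & usage). Response could then depend on baseline self-efficacy differently in the two arms. A completers-only contrast that does not condition on baseline would be biased.

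**Working it through.** **The plan's own figure.** 368/(1 - 0.20) = 460, and 368 × 1.20 = 442. The stated 450 lies within 3% of both. At exactly 20% loss, 450 × 0.80 = 360 completers, so 90 dyads would be left out of the primary analysis.

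**SD of change (not stated, so back-solved).** Inputs from Sample size: 184 per arm, 4 points, 80% power, ICC 0.03. Assumed: two-sided alpha 0.05 and 40 centres.
- Centre size 368/40 = 9.2; design effect 1 + 8.2 × 0.03 = 1.246.
- SD = 4 × √(184/1.246/2)/(1.960 + 0.842) ≈ 12.3 points. With 42 centres it is also about 12.3.

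**What a check of MCAR could detect.** Compare baseline means of 360 completers and 90 dropouts, ignoring clustering.
- SE = √(1/360 + 1/90) = 0.118 SD.
- Power at a difference d is Φ(d/0.118 - 1.96): about 13% at 0.1 SD, 40% at 0.2 SD and 72% at 0.3 SD. For 80% power, d must be about 2.80 × 0.118 = 0.33 SD.

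**Bias in one scenario.** Assumed: 30% dropout below and 10% above the baseline median in one arm, 20% throughout in the other, and correlation 0.6 between baseline and follow-up.
- Score SD = 12.3/√(2 × (1 - 0.6)) = 13.75.
- Completers' baseline mean in the first arm is too high by (0.9 - 0.7)/1.6 × 0.798 × 13.75 = 1.37 points.
- Shift in the change-score contrast (first arm minus second): (0.6 - 1) × 1.37 = -0.55 points; 0.55/4 = 14% of the target.
- Shift on an unadjusted two-month score: 0.6 × 1.37 = +0.82 points. This is less relevant, because the power model uses change.
- With baseline in the model, dropout depends only on terms that are conditioned on, and the shift disappears.

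**Range over the correlation r.** The change-score shift is -0.125 × 0.798 × 12.3 × √((1 - r)/2). This gives -0.67 at r = 0.4, -0.55 at 0.6 and -0.39 at 0.8, or 17%, 14% and 10% of four points.

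**Range over the gap.** If dropouts and completers differ in change by g SD in one arm only, the contrast shifts by 0.20 × g × 12.3. For g = 0.25, 0.5 and 1 this is about 0.6, 1.2 and 2.5 points (15%, 31% and 61% of the target).

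**Simulation without clustering.** With 450 dyads, no true effect, about 20% missing and assumed correlation 0.5, dropout depending on baseline in one arm biased the completers' change contrast by about -0.05 SD. Adjusting for baseline removed this. A pooled baseline check flagged the problem in about 53% of trials. When dropout depended on the unseen outcome, the check flagged it in about 19%, and bias remained with or without baseline adjustment.

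**The case against.** The three sentences can be read as one rule: completers if MCAR holds, imputation otherwise. Intention-to-treat is also often used to mean analysis by allocated arm, with missing outcomes handled separately. Both readings are fair, and the first is the natural one, but the article does not state it. An analysis plan that is not at hand could set a criterion. It would still have to implement or contradict a published rule that makes completers primary.

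The bias figure comes from a chosen scenario. The article gives no dropout by arm, and -0.55 is only about 0.4 of a standard error (4/2.80 = 1.43). A check made within the affected arm would do better than a pooled one: 45 dropouts against 180 completers, a gap of 0.50 SD and an SE of 0.167 SD give about 85% power in that scenario. The protocol specifies no such check.

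Three stronger readings are tempting and not supported:
- A reader might infer that the imputation ignores the centre and so gives intervals that are too narrow. The article lists no imputation variables at all, so nothing shows that centre is left out.
- A reader might infer that the choice is made on unblinded data. No timing is given, and missingness can be examined with arms masked.
- A reader might call MCAR untestable, or already false. It can be refuted from observed data, though not confirmed, and no document reports differential loss.

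**Conclusion.** The concern holds as a fault in a rule that the article states, and not as a complaint about detail left to another document. The primary analysis depends on an assumption that observed data cannot confirm. It may leave out about 90 of 450 dyads, and it stands beside two sentences whose relation to it is unclear. Under the assumed scenario, the cost is a shift of about -0.55 points in the change contrast (-0.39 to -0.67 for correlations from 0.8 to 0.4). If the affected arm is the intervention arm, its effect is understated; if it is the control arm, the effect is overstated. The size rests on the back-solved SD, the assumed correlation and the assumed dropout pattern. The fault in the rule rests on none of them.

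**What to change.** Delete the MCAR condition and name one primary analysis now: all enrolled dyads, in the arm to which their centre was allocated, by a method valid under MAR that uses baseline self-efficacy. Either of these would serve:

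- a likelihood-based mixed model of the baseline and two-month scores with a centre random effect; or
- multiple imputation that includes arm and baseline score and respects clustering by centre, followed by the planned random-effects model.

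State the role of imputation explicitly and keep completers-only as a sensitivity analysis. Because no MAR method protects against dropout driven by the unseen outcome, a delta-adjusted analysis would be a useful second sensitivity analysis.

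The cost is one reworded paragraph and slightly more programming. Baseline self-efficacy is already collected, and the sample size does not change. The wording should be settled before outcome data are analysed.

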### Effectiveness evaluation

#### Study design, recruitment, and participants

`Saga Stories in health talks´ is a cluster randomized controlled trial which will be conducted in six regions throughout Sweden (Dalarna, Norrbotten, Värmland, Västernorrland, Västra Götaland, and Örebro). The intervention group receives the health talk using Saga Stories and take-home material, whereas the control group receives the standard health talk. Eligible families are provided with oral and written information regarding the study from their CHC nurse at the routine five-year check-up. If the accompanying parent consents to participate they will scan a QR code to sign the informed consent using BankID (a secure digital signature) and directly after they will fill in the baseline questionnaire. To be included in this study, the accompanying parent needs to be able to understand and read Swedish sufficiently well in order to provide informed consent and partake in the Saga Stories health talk. There are no exclusion criteria. This study is reported according to the SPIRIT 2013 statement [12] and Table 1 shows a trial participant timeline.

**Table 1 Tab1:** Participant timeline according to SPIRIT

	STUDY PERIOD			
	Enrollment	Allocation	Post-allocation	Close-out
Time point	0	0	2 months	2 months
	5-year routine visit			

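### Randomisation was stratified by region and centre size, but neither factor is in the outcome models; if they are prognostic, the test is mildly conservative

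*Protocol article*

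**What the plan says.** Under Randomization and blinding, the protocol article states: "To ensure balance, we stratified the randomization by geographical regions and center size". The trial is "conducted in six regions throughout Sweden". Forty-two centres were randomised; after two control centres withdrew before the start, "there is 22 CHC centers in the intervention group and 18 in the control group".

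Under Statistical analyses, the comparison of arms is specified for self-efficacy, diet and screen time together: "we will use linear random-effects models, specifying the CHC center as a random effect to account for clustering". The covariates follow: "The models will be estimated unadjusted and adjusted for child age (continuous) and sex (boy vs. girl". Region and centre size are in neither version.

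Under Sample size, the power model has a random centre intercept, and "the group indicator is the only covariate".

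**The concern.** Stratified allocation balances the arms on region and centre size. Outcome variation between strata then contributes little to the true sampling error of the arm contrast. A model that omits the strata does not know this. It assigns that variation to the centre random effect and carries it into the standard error of the arm effect. The random centre intercept does not cure the problem, because that is where the excess variance ends up. Child age and sex are individual-level variables and do not stand in for region or centre size.

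At stake, if the strata are prognostic, are a confidence interval somewhat wider than it need be, a test below its nominal size, and the precision that stratifying was meant to bring.

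**Working it through.** **Inputs**

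- Centres: 40 (22 and 18), from Randomization and blinding.
- Regions: 6, from Study design. The number of centre-size categories is not stated: 2 assumed in the simulation, 2 or 3 when counting degrees of freedom.
- ICC: "under an assumed intra-center correlation of 0.03" (Sample size).
- Evaluable dyads: 368, or 184 per arm (Sample size), so m = 368/40 = 9.2 per centre.
- Target: "statistical power of 80% to detect a four-point difference in parental self-efficacy between the two treatment groups".
- Not given: the significance level (two-sided 0.05 assumed), the residual SD (back-solved below), and the share f of between-centre variance that the strata explain (taken over its full range, 0 to 100%).

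**Step 1: the plan's own figure.** The 368 cannot be reproduced independently without the SD and significance level. Back-solving:

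- Design effect = 1 + (9.2 - 1) × 0.03 = 1.246
- SD = 4 / [(1.960 + 0.842) × √(2 × 1.246/184)] = 4 / (2.802 × 0.1164) = about 12.3 points
- With that SD, 148 per arm under individual randomisation × 1.246 = 184 per arm

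This shows consistency only. The standard-error ratios in step 2 do not depend on the SD.

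**Step 2: closed form.** In units of the total variance, a centre mean has variance 0.03 + 0.97/9.2 = 0.1354 as the unadjusted model sees it. Once the strata are accounted for, it is 0.03(1 - f) + 0.97/9.2. The standard-error ratio (adjusted to unadjusted) is the square root of the second over the first, and the overstatement is 1/ratio - 1. The unadjusted type I error is 2Φ(-1.96/ratio).

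| f | Variance | SE ratio | SE overstated by | Type I error, unadjusted | Power, unadjusted / adjusted |
|---|---|---|---|---|---|
| 0% | 0.1354 | 1.000 | 0% | 5.0% | 80.0% / 80.0% |
| 25% | 0.1279 | 0.972 | 3% | 4.4% | 80.7% / 82.2% |
| 50% | 0.1204 | 0.943 | 6% | 3.8% | 81.4% / 84.4% |
| 100% | 0.1054 | 0.882 | 13% | 2.6% | 83.0% / 88.8% |

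The small ICC caps the effect: even if the strata explain every difference between centres, they remove only 0.03 of 0.1354. This version uses normal quantiles and assumes perfect balance, so it is an outer bound.

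**Step 3: simulation.** Centre means were simulated for 40 equal-sized centres in 6 regions × 2 size classes, allocated within strata and treated as roughly 1:1. There were 40,000 runs per scenario, with t-tests on 38 degrees of freedom (unadjusted) and 32 (adjusted).

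| f | Type I error, unadjusted / adjusted | Power, unadjusted / adjusted | Change in power |
|---|---|---|---|
| 0% | 5.1% / 5.2% | 78.2% / 77.2% | -1.0 |
| 25% | 4.5% / 4.9% | 79.0% / 79.2% | +0.2 |
| 50% | 4.2% / 4.9% | 79.7% / 81.4% | +1.7 |
| 100% | 3.4% / 5.1% | 81.8% / 86.2% | +4.4 |

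Simulation error is about √(0.05 × 0.95/40,000) = 0.1 point for type I error and √(0.8 × 0.2/40,000) = 0.2 point for each power, so the +0.2 is not clearly different from zero.

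The simulation is milder than the closed form for three reasons. It uses t quantiles. Odd-sized strata cannot be split evenly. It also draws the region and size effects at random, with 70% of stratum variance for region and 30% for size, so the realised stratum variance averages about 0.7 × 5/6 + 0.3 × 1/2 = 0.73 of its nominal value.

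**Step 4: cost of adjusting.** Region takes 5 degrees of freedom and centre size 1 or 2, so 6 or 7 of 40 - 2 = 38. From the non-central t distribution with f = 0, that loss alone moves power from 77.9% to 77.5%. The full 1 point in the simulation also reflects the imperfect split within strata.

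**The case against.** The case for leaving the models alone has four parts.

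1. **The harm is conditional.** It exists only if region or centre size predicts the outcome, and the article gives no figure for that. At f = 0 the unadjusted test has its nominal size and adjusting costs about 1 point of power. A reader might infer that the standard errors are definitely wrong. The documents do not support that, and zero belongs in the range.
2. **Nothing is lost against the plan.** A reader might infer that the stated 80% power is eroded. It is not: the power model had group as its only covariate, which is how the unadjusted analysis is specified. Any error is conservative. No bias in the treatment effect is shown, and false positives are not inflated.
3. **The lost centres prove nothing here.** A reader might infer that losing two control centres upset the stratum balance and that adjustment would repair it. The article does not give their region or size, so neither step can be shown. If balance had been upset, the unadjusted test would also be less conservative than calculated above.
4. **This is an article.** An analysis plan that is not shown may add the factors, and the degrees-of-freedom method is properly left to it.

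The first three stand and limit the size of the point. The fourth stands for the degrees-of-freedom method but does not remove the mismatch. The article is not silent on covariates: it lists them down to their coding, and the list leaves out both factors that restricted the randomisation.

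**Conclusion.** The mismatch between design and analysis is plain in the text; its effect is small and conditional. At an ICC of 0.03 with about 9 completers in each of 40 centres, leaving out the strata overstates the standard error by 0 to 13% (about 6% if they explain half of the between-centre variance). The unadjusted model's type I error is about 5.1% falling to 3.4%. Adjusting changes power by about -1 to +4 points, about +2 at half; the closed form puts the extreme at nearly +6 (88.8 - 83.0 = 5.8). What may be forgone is some precision and a test at its nominal size, not the planned power.

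This rests on an assumed two-sided 5% level, a back-solved SD, an unknown share f, an assumed number of size classes and equal centre sizes. The ICC is stated only in the self-efficacy calculation. None is given for diet or screen time, where a larger value would widen the range. This is a cheap improvement, not a flaw that threatens the trial's conclusion.

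**What to change.** Add geographical region (six levels) and the centre-size category used at randomisation as fixed effects in the primary and secondary outcome models, alongside the random centre intercept. State the size categories. Child age and sex can stay in the adjusted version as planned.

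The cost is one clause of text and 6 or 7 between-centre degrees of freedom. If the strata turn out not to be prognostic, that means about 1 point of power. No new data are needed, because both factors were already known at allocation, and the sample size does not change. The change should be made before outcome data are compared by arm.
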